**Figure 1 F1:**
[figure not shown]
Study protocol flowchart.

The assignment to one of the two arms will not be disclosed to the participants and to the experimenters who will interface with the subjects for consultation and psychological assessment through questionnaires. Only personnel who analyze the data collected from the study will be aware of participants who receive psychological support consultation. Participants will be randomized during T0 assessment, immediately after the collection of socio-demographic and clinical data and psychological measures.

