### Study design and setting

This study will be conducted at the European Institute of Oncology of Milan (Italy). The IEO is a specialized Hospital and internationally recognized Cancer Center located in Italy working on research, prevention, diagnosis, and treatment of cancer. The IEO offers to the patients innovative and personalized care, from the diagnosis onward. Study design is longitudinal randomized, with a 1:1 allocation ration analyzing the proposed primary and secondary aims.

Participants will be randomly assigned to one of the two following arms: (1) dyads receiving a psychological support consultation (experimental group); (2) dyads receiving no psychological support consultation (control group). For ethical reasons, the dyads in the control group will be offered the option to receive the psychological support consultation at the end of the study, but only in case the psychological support consultation turns out to be beneficial for the dyads. Indeed, the study did not foresee a cross sectional design.

The dyads assigned to the experimental group will be contacted by the clinical psychologist to schedule an appointment for the psychological support consultation. The consultation will be performed within the period of diagnostic assessment, preferably within the date of pre-hospitalization for surgery or for starting other cancer treatments. The consultation will be carried out by a clinical psychologist with a master's degree in clinical psychology, a state certificate exam, and previous internship in psychological support intervention for cancer patients.

The consultation will last 60 min and will include the following steps and areas of focus:

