- the psychologist will open the consultation by asking the dyads if they would like to narrate their emotional reaction to the cancer diagnosis, if they were together when they got the bad news or if the patients later communicated diagnosis to the caregivers. This way, the psychologist can start sharing their emotional state of the dyads and their communication style;- then, the psychologist will assess the dyad's preferences about their mutual involvement in the clinical assessment path (e.g., participating together in medical examinations) and in the decision-making process, and their level of agreement regarding the ideal care path. The psychologist can help dyads to explicit their emotional status, have an effective and assertive exchange of ideas, provide different input on how to handle the upcoming star of treatments. Moreover, the psychologist will evaluate their feelings and perception about the relationship with the medical team to assess whether a therapeutic alliance between patients, caregivers and clinicians can be structured.- finally, the psychologist will help them in reporting their emotions/fears and mutual needs, to help the dyad go through this difficult moment of life together providing adequate support to each other. During the consultation, the psychologist will be available to address even more topics of interest to the dyad to favor the care path and a better quality of life, such as how to behave with minor children or with extended family.

The psychologist who is going to carry out the consultations will be supervised by a coordinator with a specialization in psychotherapy, with the aim of solving any doubts.

The evaluation through a set of standardized questionnaire swill be carried out at three time points: initial evaluation before randomization (baseline, pre-consultation; T0), after the pre-hospitalization (and post psychological consultation for the experimental group; T1), at 6 months after the beginning of the medical treatment (T2). Between the baseline evaluation (T0) and the second evaluation (T1), the experimental group will meet the psychologist for the consultation and the control group will not receive any intervention, but both groups will have made decision about cancer treatments with their referring oncologists. The average time between the two assessment T0 and T1 is about 4 weeks (see Figure 1 for the study flowchart).

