Notwithstanding, it is necessary to mention some of the limitations that can be linked to this study. First, the inclusion of caregivers with different relationships with patients (all possible dyads are included) can create non-homogeneity in the sample composition, as there may be specific relationship factors that influence the results. In addition, there may be a large loss of participants in the control group, that might not see any direct advantage in participating, so it may be strategic to remind them that they may require hospital-provided psychological support at the end of the study (albeit for a fee).

Despite these limitations, the results that are expected to be obtained after conducting this trial may be useful in helping patients-caregivers' dyads during the cancer care path to reduce possible disagreement within the dyads and enhance patients' adherence to cure and the satisfaction with the decision made and more in general to better their daily life.

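### The blinding paragraph says participants and psychologist will not know the arm, which the design makes impossible, and leaves unblinded the analysts, who could easily be blinded

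*Protocol article*

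**What the plan says.** The statement stands in the protocol article, Study design and setting, in the paragraph after Figure 1. The allocation, it says, "will not be disclosed to the participants and to the experimenters who will interface with the subjects for consultation". The same sentence goes on to cover the questionnaire assessments, so the staff kept unaware include those who deliver the consultation as well as those who handle the questionnaires. The next sentence reads: "Only personnel who analyze the data collected from the study will be aware of participants who receive psychological support consultation".

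Earlier in the same section the procedure is: "The dyads assigned to the experimental group will be contacted by the clinical psychologist to schedule an appointment for the psychological support consultation". The session lasts 60 minutes and follows set steps. For the other arm, "the control group will not receive any intervention" between T0 and T1. Control dyads are to be offered the consultation when the study ends, if it has proved beneficial.

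The limitations paragraph of the Discussion expects that many controls may be lost because they might see no direct advantage in taking part. It suggests reminding them that psychological support can be had from the hospital at the end of the study, for a fee.

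**The concern.** The masking described is one the design cannot have. A dyad that attends an hour with a psychologist knows that it did so. A psychologist who is given only experimental dyads to call knows which arm they are in. The analysts are the group most easily kept unaware, yet they are the only group said to be aware.

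Two things are at stake. First, a reader who takes the paragraph at its word would credit the trial with blinded self-report. In fact the comparison is an open one, consultation against nothing, in which expectation can shift the answers, most plausibly in favour of the treated arm. Second, blinded analysis protects against choosing a method because of the result it gives. The plan gives up that protection without stating a reason, although Data analyses leaves some choices to be made after the data are seen.

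**Working it through.** No figure in the protocol is in dispute here, so the check is mainly a comparison of passages.

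**1. Can participants be unaware?** Study design and setting gives one arm a 60-minute consultation and the other no intervention. No sham or attention session is described. Under Participants, patients are told the purposes and procedure of the study at first contact. Experimental dyads therefore know their arm, and controls can infer theirs. The Discussion presumes the same, since controls who did not know their arm would have no arm-specific reason to leave.

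**2. Can the psychologist be unaware?** The psychologist contacts only dyads assigned to the experimental group, so the contact list is the allocation list.

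**3. Can the paragraph be read another way?**
- *Concealment before randomisation.* The text speaks of not disclosing the assignment itself and of who knows which participants receive the consultation. Both concern the time after assignment.
- *Questionnaire staff only.* The sentence names the consultation explicitly.
- *The arm label is withheld.* Dyads and psychologist would still know what was given, and the claim that only analysts know would still be untrue.

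**4. Which outcomes are exposed?** Every measure listed at T1 and T2 in Table 1 is a questionnaire answered by patients or caregivers: CPS, decisional role, PAIR, HADS, MSPSS, SF-12, SDM-Q-9, CARE, SWD and ADQ. The MBSS is taken only at T0, before randomisation, and is not exposed.

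**5. The plan's own figures, for scale.** Sample size and power calculation gives a difference of 3 points, SD about 5, two-sided alpha 0.05, 80% power and 44 per arm.
- n per arm = 2 × (1.960 + 0.842)² × (5/3)² = 43.6, rounded up to 44, or 88 in total. This reproduces the plan's figure (normal approximation).
- Standard error of the difference at 44 per arm = 5 × √(2/44) = 1.066 points.

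**6. Illustration with an assumed bias.** Let the true effect be zero and let unblinded self-report shift the difference by b points. Then P(reject) = Φ(b/1.066 − 1.960) + Φ(−b/1.066 − 1.960).

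| Assumed b (points) | In SD (b/5) | Share of the 3-point target | Two-sided rejection rate |
|---|---|---|---|
| 0 | 0 | 0 | 5% |
| 0.5 | 0.1 | 17% | 7.6% |
| 1.0 | 0.2 | 33% | 15.5% |
| 1.5 | 0.3 | 50% | 29% |

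The values of b are assumptions. The protocol gives nothing from which to estimate them.

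**The case against.** The strongest reply is that the article never uses the words blind or masked. It says only that assignment will not be disclosed, and it describes consultation against no intervention openly enough for a careful reader to see that the trial is open. That is fair as to vocabulary, but it does not rescue the sentence that restricts knowledge of the arm to the analysts, which is false on any reading.

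A second reply is that analysts knowing the arm contradicts nothing in the document, and that coding the arms is good practice rather than the correction of an error. It is true that this half is a design choice and not a contradiction. It is also true that the scope for choice in the analysis should not be overstated. The rank-test option is tied to a check of skewness and kurtosis, exclusion is tied to a completion rule, and a separate analysis plan may fix the cut-offs. What remains in this document is a choice between non-parametric tests and SEM for non-normal data, and an exclusion rule that can be read as missing either later visit or both. Unblinded analysis is still stated as the design, with nothing gained by it.

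A third reply is that the size of any bias is assumed, and that the ADQ is collected six months after treatment begins, following a single session, so that expectation may have faded by then. This stands: neither the size nor the direction of bias can be established from the document.

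**Conclusion.** The concern holds. The statement that participants and consultation staff will not know the arm is incompatible with the procedures in the same section, and no other part of the article corrects it. Unblinded participants are unavoidable with this intervention and are not the fault. The fault is to state otherwise, to omit unblinded self-report from the limitations, and to leave the analysts unblinded.

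All outcomes measured after randomisation are exposed, including the ADQ subscales on which the trial is sized. The bias cannot be quantified from the protocol. The rejection rates of 7.6% to 29% rest wholly on an assumed shift of 0.1 to 0.3 SD with no true effect, and the conclusion does not depend on them. The model and the sample size are unaffected. The correction should be made, but it does not call the design itself into question.

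**What to change.** Replace the blinding sentences after Figure 1 with text to this effect:

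> Participants and the psychologist who delivers the consultation are not blinded. T1 and T2 questionnaire links are sent automatically through the survey platform by staff who have no access to the allocation. The data analyst works with arms coded A and B, and the code is held by the data manager until the primary analysis is final.

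Add to the limitations in the Discussion that outcomes are self-reported by participants who know their arm and are compared with no intervention, and word the conclusions accordingly.

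The correction itself costs a few sentences. Coding the arms costs one recoded variable and someone other than the analyst to hold the key. The protocol describes online completion explicitly at T0, so the sponsor should confirm that T1 and T2 links can be sent the same way. If so, the added work is small. Sample size, intervention and visit schedule stay as they are.

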## Measures

### Time 0 assessment

Before the randomization, all the dyads will fill out a set of questionnaires separately, administered electronically *via* the Qualtrics™ online platform. A specific link to the survey will be created and provided *via* email or mobile phone to the personal email or telephone number of the patients and the caregivers. In the mail text, the researcher reminded the patients and caregivers to fill out the survey autonomously stressing the importance of answering in a personal and sincere way. The survey will take about 30 min to complete (assessed in a pilot with 5 dyads) and will include the following domains and related measures:

#### Demographic

Gender, age, education, occupation, origin, degree of relationship with the patient or caregiver.

#### Decisional role preference

A modified version of the Control Preference Scale questionnaire (Degner et al., 1997) is administered to examine patients' and caregivers' preference for caregiver involvement in cancer TDM, as used in other studies (Giordano et al., 2008; Shin et al., 2013, 2017, 2018). One item evaluates patients' and caregivers' desirable level of caregivers' involvement in TDM. Response options are 5 that refer to an active, collaborative, or passive role in TDM.

#### Dyadic communication

Five items from the Personal Assessment of Intimacy in Relationships scale [PAIR (Schaefer and Olson, 1981)] will be included to evaluate dyadic communication (3 items from the emotional intimacy subscale and 2 items from the intellectual intimacy subscale). These items are measured on a 5-point Likert scale, from 1 = does not describe me/my relationship at all to 5 = describes me/my relationship very well. Scores can be interpreted in terms of the difference between the dyads' scores. Every participant can decide for him/her-self what is good or ideal. The internal reliability coefficient (Cronbach α) of the communication subscale of PAIR is 0.80 (Constant).

#### Coping style

The Miller Behavioral Style Scale [MBSS (Miller, 1987)] is a coping style measure used to determine the information-seeking behaviors of individuals under threat. It is composed of 32 items and aims at differentiating between individuals who actively seek threat-relevant information (monitoring style) and those who distract themselves from threatening information (blunting style). Four imaginary stress evoking situations are described (i.e., a dentist, hostage, redundancy, and airplane scenario) and participants can choose all responses (8 responses) that they think are most characteristic of how they would act in each situation. Four responses referred to the monitoring style and four to the blunting style. This psychological variable can be considered a trait variable that remains stable over time. Cronbach's α coefficients for the monitoring and blunting sub-scales were 0.65 and 0.41, respectively (Rees and Bath, 2000).

#### Anxiety and depression

The Hospital Anxiety and Depression Scale [HADS (Zigmond and Snaith, 1983)] is a self-administered measure used to screen for the presence of anxiety and depression. It consists of 14 items on a person's mood in the past week. Seven items assess depression, referring to anhedonia (an inability to experience pleasure) and to the appearance and feelings of slowing down. Seven items assess anxiety, both autonomic anxiety (panic and butterflies in the stomach), and tension and restlessness (Dunbar et al., 2000). Each item is rated on a 4-point scale for a total score ranging from 0 to 21 for each subscale. A higher score indicates higher distress and the cut-off points for establishing the presence of anxiety and depression is set at 8. This scale has been adapted and validated into Italian both for cancer patients and a community sample (Annunziata et al., 2011; Iani et al., 2014).

#### Perceived social support

The Multidimensional Scale of Perceived Social Support [MSPSS (Zimet et al., 1988)] consists of 12 items measuring the perceived adequacy of social support from three factors: Family, Friends, and Significant Others. The respondents are asked to indicate their level of agreement to each item on a seven-point Likert scale (1 = strongly disagree to 7 = strongly agree). This scale has been adapted and validated in Italian by Di Fabio and Palazzeschi (2015), showing an internal consistency (Cronbach's α coefficients) of 0.89 (Fabio and Busoni, 2009).

#### Health status

The SF-12 Health Survey is a shortened version of the SF-36, created to reduce the burden of response (Ware et al., 1996; Jenkinson et al., 1997; Gandek et al., 1998). The SF-12 is a self-reported outcome measure assessing the impact of health on an individual's everyday life and it is often used as a quality-of-life measure. It is composed of 12 items, extracted from the SF-36, and related to the same domains of SF-36. In particular, the following domains are evaluated by two items: limitations in physical activities because of health problems; limitations in social activities because of physical or emotional problems; limitations in usual role activities because of physical health problems and limitations in usual role activities because of emotional problems. Instead, bodily pain, general mental health (psychological distress and wellbeing), vitality (energy and fatigue) and general health perceptions are evaluated by one item. Subjects are asked to answer by evaluating the day they completed the questionnaire and the previous 4 weeks. The scoring provides two summary measures related to physical and mental health (PCS-12 and MCS-12). Kodraliu et al. (2001) assessed the SF-12 in various Italian settings, including the general population and specific patient groups, showing that the SF-12 has good validity.

#### Shared decision-making

The Shared Decision-Making Questionnaire (SDM-Q-9) was developed in a theory-driven manner and measures the extent to which patients are involved in the process of decision-making from the perspective of the patient [patient version SDM-Q-9 (Kriston et al., 2010)]. It is composed of 9 items/statements, which can be rated on a six-point Likert scale from “completely disagree” (0) to “completely agree” (5). The questionnaire will be adapted for the caregivers involved in the following study. The SDM-Q-9 was translated into English and Italian, allowing for use in international research (Kriston et al., 2010). The questionnaire was validated in a psychiatric clinical sample showing a Cronbach's α coefficient of 0.86 (de Filippis et al., 2022).

#### Empathy toward physicians

The Consultation and Relational Empathy (CARE) Measure (Mercer, 2004) is a person-centered process measure composed of 10 items. It measures empathy in the context of the therapeutic relationship during a one-on-one consultation between a clinician and a patient. Participants are asked to evaluate how the doctor was in some situations on a six-point Likert scale, ranging from poor (0) to excellent (5) or does not apply (6). The tool will be adapted for the caregivers involved in the following study. The Italian version of the CARE measure showed high internal reliability (Cronbach's α = 0.962) (Natali et al., 2022).

### T1 measures

#### Decisional role preference

An original modified version of the Control Preference Scale questionnaire (Degner et al., 1997) is administered estimating the actual level of caregivers' involvement in TDM from patients and caregivers' perspectives.

#### Decisional role

An Italian translation of original questions drafted by Shin et al. (2017) are included to investigate the patient's perceived benefit/harm of caregiver's involvement in TDM. First, respondents were asked to rate the level of family involvement regarding communication, treatment decisions, and psychological support on a 3-point Likert scale: harmful, neither harmful nor helpful, or helpful (Original items were: “family involvement is—harmful, neither harmful nor helpful, helpful—for communication, treatment decision, psychological support”). Then, respondents were also asked to indicate their level of agreement on a 4-point Likert scale (from 1 = strongly disagree to 4 = strongly agree) with the following statements regarding family involvement in cancer TDM: “It hampers patient autonomy,” “it complicates the cancer TDM process,” and “it leads to a harmonious decision,” and “Families have the right to be involved.”

#### Satisfaction with decisions

The Satisfaction with Decision scale (SWD) measures the satisfaction with health care decisions (Holmes-Rovner et al., 1996). It consists of 6 items rated on a five-point Likert scale from “strongly disagree” (1) to “strongly agree” (5). The tool will be adapted for the caregivers involved in the following study. The scale has excellent reliability (Cronbach's alpha = 0.86).

The following questionnaires administered at T0 will be also included also at T1, to evaluate the change in the psychological status: The Hospital Anxiety and Depression Scale [HADS (Zigmond and Snaith, 1983)]; The Multidimensional Scale of Perceived Social Support [MSPSS (Zimet et al., 1988)]; The SF-12 Health Survey (Ware et al., 1996); The 9-item Shared Decision-Making Questionnaire [SDM-Q-9 (Kriston et al., 2010)]; The Consultation and Relational Empathy (CARE) Measure (Mercer, 2004).

### T2 measures

#### Adherence to therapies

The Adherence Determinants Questionnaire [ADQ (DiMatteo et al., 1993)] is a multifactorial tool aiming at evaluating the elements of patients' self-adherence to cancer treatments, taking into consideration a set of cognitive and motivational skills, as well as social and behavioral variables. Response options for each item comprise 5-point Likert scales (1 = *strongly disagree;* 2 = *disagree;* 3 = *neither agree nor disagree;* 4 = *agree; 5* = *strongly agree*). Seven subscales are considered: Interpersonal Aspects of Care; Perceived Utility (Benefits/Costs and Efficacy); Perceived Severity; Perceived Susceptibility; Subjective Norms; Intentions; Support/Barriers. The components of the ADQ were found to be generally reliable (median alpha reliability = 0.76) (DiMatteo et al., 1993).

In addition, the following questionnaires will be re-administered: item from Shin and colleagues (Shin et al., 2017) for Decisional Role; 5 items from PAIR (Schaefer and Olson, 1981) (dyadic communication); The HADS (Zigmond and Snaith, 1983); The MSPSS (Zimet et al., 1988); The SF-12 Health Survey (Ware et al., 1996); The SWD (Holmes-Rovner et al., 1996).

